### 10.3. Analysis of Outcome Measures

All outcomes will be presented using descriptive statistics; normally distributed data by the mean and standard deviation and skewed distributions by the median and interquartile range. Binary variables will be presented using counts and percentages. We will summarise descriptive data using CONSORT reporting standards for RCTs. STATA will be used for statistical analysis.

#### 10.3.1. Primary outcome

Gestational diabetes incidence will be analysed as risk ratios and risk differences will be estimated by binary regression and results presented as odds ratio and 95% confidence interval.

Date and version No: 18th July 2019, Version 4.2

A covariate adjusted analysis of the effect of treatment on the primary outcome will be undertaken to remove bias from the estimate of the treatment effect on the primary outcome.

We will also test for the difference in effects on GDM incidence between the centres. If the odds ratio (OR) for GDM associated with the intervention in The Gambia is ORG, and in India is ORI, then the ratio of these two terms measures the difference in effect.

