## 10.2. The Number of Participants

The sample size is 1856 high-risk women (928 to be recruited in The Gambia and India). The study was powered to have 80% to detect a 33% reduction in the incidence of GDM, for the main effects of diet and PA, with a family-wise significance level of 5% for a two-sided test (i.e. each effect was tested at a significance level of 2.5%). It was assumed that participants could be pooled across centres (no interaction between interventions and country at the 5% level). The sample size was inflated to allow for a 15% drop out rate in each of the four strata, with drop outs defined as non-compliant participants (i.e. no risk reduction in their incidence of GDM).

The effect sizes for the sample size calculation were:

Prevalence of GDM in high-risk pregnant women: The largest study of GDM women (The HAPO study, 25,505 pregnant women unselected for GDM risk at 15 centres in nine countries) reported a GDM prevalence rate, based on IADPSG criteria, of 17.8% among the general population. In our 'high-risk' population, we assume that the prevalence will be higher than in the HAPO study. Therefore, we have estimated the prevalence of 25% in our study.

Estimated risk reduction: A recent meta-analysis (Song et al. Obesity reviews 2016) has shown that either diet or PA results in 18% (95% CI 5-30%) risk reduction in GDM in general pregnant population and interventions as early as 15 weeks of gestational age was also associated with reduced GDM risk (Relative risk: 0.80, 95%CI 0.66-0.97). Putting all these together, we estimate the risk reduction would be higher (about 1/3, 33%) in this high-risk population. We modelled the GDM percentages in four equal-sized combinations of control (c) and treatment (t) arms as 25% (c-c), 16.75% (c-t and t-c) and 11.2 in t-t group. Therefore, in simple comparisons of one exposure, the percentages will be 20.9% vs 13.0%.

Absence of intervention\*country interaction: In order to pool the participants of both countries, we will be assuming that there are no differences between the participants of both countries. This initial test for a non-significant interaction term (at the 5% level) between each intervention and country was also taken into account in the sample size simulation.

The sample size calculation was performed by simulation (in R version 3.5.2) according to the following algorithm:

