1. For a given sample size, we generated 8 subgroups, two (one per country) for each intervention combination (control-control, treatment1-control, control-treatment2, treatment1-treatment2).
2. For each subgroup we generated the expected GDM incidence, except for a random 15% (drop-outs), whose expected GDM incidence was considered to be 25% (corresponding to the control group) regardless of their originally allocated subgroup.

Date and version No: 18th July 2019, Version 4.2

3. We first tested if either the interaction term site\*PA or site\*Yoghurt was statistically significant (at the 5% level).
4. If the assumption of no intervention\*country interaction was met, we recorded for each intervention if it was statistically significant (at the 2.5%, as we were doing two tests, one for each intervention), assuming a two-sided test
5. This was repeated 10,000 times.
6. The % of repetitions with statistically significant intervention effects represents the power associated with the sample size.
7. Steps 1-6 were repeated for increasing sample sizes.
8. A smoothed (lowess) line was fitted.
9. The point where this line crossed the 80% power mark gave us the final sample size required. (Figure 1)

[figure not shown]

Figure 1: Estimated power for increasing sample size, with an estimated risk reduction of 33%,  $\alpha = 0.05$  and estimated drop-out rate of 15% (based on 10,000 iterations).

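### Section 10.3.1 estimates risk ratios and risk differences but presents an odds ratio, with a 95% interval that does not match the 2.5% test per intervention

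*Protocol*

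**What the plan says.** Section 10.3.1 (Primary outcome) states that "risk ratios and risk differences will be estimated by binary regression and results presented as odds ratio and 95% confidence interval". It then defines the difference in effect between the two centres as a ratio of odds ratios. It gives no significance level for the two main effects.

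Section 10.2 (The Number of Participants) is written on the risk scale. The trial is powered at "80% to detect a 33% reduction in the incidence of GDM, for the main effects of diet and PA", and the four arms are modelled as "25% (c-c), 16.75% (c-t and t-c) and 11.2 in t-t group". The error rate is set there too: "with a family-wise significance level of 5% for a two-sided test (i.e. each effect was tested at a significance level of 2.5"%). Step 4 of the simulation algorithm repeats the level: "at the 2.5%, as we were doing two tests, one for each intervention". The caption of the power figure in the same section gives α as 0.05 and does not say whether this is per test or family-wise.

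**The concern.** There are two mismatches, both inside this one document.

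- **Effect measure.** A statistician following section 10.3.1 cannot tell whether the headline result is the risk ratio, the risk difference or the odds ratio. The protocol does not leave this open for a later analysis plan; it fixes the point in two incompatible ways. An odds ratio also cannot be set directly against the 33% reduction that the trial was designed to detect.
- **Interval and test.** The design spends 2.5% on each intervention, while the primary result is to carry a 95% interval. A reader of section 10.3.1 alone would naturally take an interval that excludes 1 as a positive result, which is a 5% test per intervention.

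The trial is open label, so it is worth having the headline measure and the criterion for a positive result settled beforehand, so that neither can be chosen after the data are seen.

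**Working it through.** **Inputs (all from protocol section 10.2).** Control-cell risk 25%; relative reduction 33%, i.e. risk ratio (RR) 0.67; four equal arms; 15% drop-outs who keep a 25% risk; N = 1856, so 928 women at each level of each factor; two-sided 2.5% per intervention.

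**1. Reproducing the plan's own figures**
- Cells: 25 × 0.67 = 16.75 and 16.75 × 0.67 = 11.22, printed as 11.2. The model is multiplicative in risk, so the design scale is the RR.
- Margins: (25 + 16.75)/2 = 20.9, as printed. (16.75 + 11.2)/2 = 14.0, whereas the protocol prints 13.0. The cell-derived 14.0 is used below.
- Sample size: simulating the stated algorithm at N = 1856 gives 80.2% power per effect, if an effect counts when it is significant at 2.5% and its own site interaction is not significant at 5%. If both interaction terms must be non-significant it gives 76.2%. The stated N is therefore reproduced under the first reading, and nothing below alters it.

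**2. Odds ratio against risk ratio**

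OR = [p1/(1 − p1)] / [p0/(1 − p0)]; RR = p1/p0.

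| Comparison | RR | OR |
|---|---|---|
| Single cell, 16.75% vs 25% | 0.67 | 0.2012/0.3333 = 0.604 |
| Margins from the cells, 14.0% vs 20.9% | 0.67 | 0.616 |
| Margins with 15% drop-outs, 15.6% vs 21.5% | 0.73 | 0.68 |

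The last row uses 0.85 × 20.875 + 0.15 × 25 = 21.49 and 0.85 × 13.98 + 0.15 × 25 = 15.63. The same data are thus a 33% lower risk or 38–40% lower odds and, with drop-outs, a 27% lower risk or 32% lower odds. With the printed 13.0% the margins would give RR 0.62 and OR 0.57, so the gap remains.

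**3. 95% interval against the 2.5% test**
- Critical values: z = 1.960 for a 95% interval and 2.241 for a 97.5% interval. Ratio 2.241/1.960 = 1.14.
- Family-wise error if two independent null effects are each judged by a 95% interval: 1 − 0.95² = 9.75%. At 2.5% each: 1 − 0.975² = 4.94%.
- Worked case: comparator risk 21.5%, 928 per level, observed RR 0.82, so the other risk is 17.6%. SE(log RR) = √[(1 − 0.215)/(928 × 0.215) + (1 − 0.176)/(928 × 0.176)] ≈ 0.095, so z = 0.198/0.0947 = 2.095 and p = 0.036. The 95% interval is 0.681–0.987 and the 97.5% interval is 0.663–1.014. The presented interval excludes 1 while the planned test is not met.
- Frequency: in simulation at N = 1856, p falls between 0.025 and 0.05 for about 6% of results per intervention under the design assumptions, and for about 2.4% under the null.

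**The case against.** Several points on the other side are sound.

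- A reader might infer that the plan omits the risk ratio. It does not: the same sentence commits to estimating risk ratios and risk differences, and section 10.3 promises counts and percentages for binary variables. The defect is a contradiction about what is presented.
- A reader might infer that an odds ratio overstates the effect. An odds ratio labelled as one is correct, and OR 0.62 and RR 0.67 describe the same data. Misreading arises only if the odds ratio is taken for a risk reduction or compared with the 33% target.
- A reader might infer that control of the family-wise error is lost outright. The documents do not support that. The only decision rule stated is two-sided 2.5% per intervention, and section 10.3.1 nowhere says that significance is read from whether the 95% interval excludes 1. A 95% interval is acceptable as description. The 9.75% applies only if the intervals are used to decide.
- A ratio of odds ratios is a coherent way to compare centres, and sizing on a relative reduction does not by itself oblige anyone to report risk ratios.

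Two things remain. The protocol names incompatible primary measures in one sentence. The section that governs the primary analysis gives an interval at a different level from the stated test and does not say which governs.

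**Conclusion.** The point holds as an internal contradiction on the primary effect measure and a mismatch between the presented interval and the stated test level. On the protocol's own rates the choice of scale moves the planned effect from 0.67 (risk ratio) to 0.60–0.62 (odds ratio), or from 0.73 to 0.68 after the planned drop-out. Reading both results from 95% intervals would give a family-wise error of about 9.75% against the designed 4.9%. These figures assume the 25% control risk, the multiplicative cell rates with 14.0% derived in place of the printed 13.0%, and near-independent tests of the two factors, as expected in a balanced factorial. The error-rate consequence is conditional on how the intervals are used. The ambiguity about the measure is not conditional on anything.

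**What to change.** Replace the sentence in section 10.3.1 along these lines: For each intervention the risk ratio (primary measure) and the risk difference will be estimated from a binary regression model containing both factors. Each main effect will be tested at the two-sided 2.5% level, and 97.5% confidence intervals will be given for the two main effects.

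95% intervals may be shown as well if they are labelled descriptive. The odds ratio may be kept as supplementary. The between-centre ratio of odds ratios may stay, or be given as a ratio of risk ratios for consistency. When section 10.2 is next edited, reconcile the printed 13.0% with the cell rates, and say in the caption of the power figure that α = 0.05 is family-wise.

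The cost is one sentence and intervals about 14% wider on the log scale, which the stated 2.5% level already implies. Sample size, data collection and the planned tests are unchanged. The change should be made before any comparison by arm is seen.

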### **10.3.2. Secondary outcomes**

The secondary outcomes will compare the difference in fasting plasma glucose at week 32, gestational weight gain, intrapartum and neonatal outcomes between the intervention and control groups. Continuous variables will be analysed using multiple linear regression and binary variables by logistic regression and adjusted for pre-specified covariates.

### **10.3.3. Safety**

The incidence rates of AEs and SAEs and their relationship to trial interventions will be summarised by intervention group. The proportion of women discontinuing treatment will be summarised by reason and by intervention group.

## **11. DATA MANAGEMENT**

All protocol required data will be captured in electronic Case Report forms (eCRF) that will be completed for each included participant by trial personnel. Data will be regularly checked by the Data Manager. On the eCRF, a reference to the source document will be provided. Instructions for completing all forms, including the CRF, used in the study will be developed. All data will be entered onto a secured, password-protected database that will only be accessed by the data manager and designated investigators.

### **11.1. Types of data**

The study will include collection of both research (quantitative and qualitative) and personal data. Data minimisation has been considered and thus personal data will only include name, addresses and telephone number collected for the purpose of telephonic follow-ups/reminders and home visits by the field staff for the current study. These data will however be also used if the participant needs to be contacted for future approved studies (follow-up of babies born to high-risk GDM mothers). Personal information will be available only to the study PI and designated staff involved in contacting the participants either telephonically or by home visits. As this study has the potential to be extended in the future for other follow-up studies, personal data will pseudonymised and stored locally at their study centres. There will be no transfer/sharing of personal data outside the study centre. This personal data will be not be linked to research data and will be maintained in separate files at each study centre and will be password protected and accessible only to authorized staff of the study team.

### **11.2. Format and scale of data**

REDCap software will be used in the trial. It is a secure web application for building and managing databases. The final data format will be downloaded to Excel and common statistical packages (SPSS, SAS, Stata, R). REDCap is specifically geared to support online or offline data

Date and version No: 18th July 2019, Version 4.2

capture for research studies and operations. This data management system is a fully supported, externally validated (GCP compliant to 21 CFR parts 11) clinical database. The database will be hosted and managed by the MRCG and the final tested production database will be shared with the partner site in India who will enter/synchronize data into the central database.

### **11.3. Data collection/generation**

Research data will be collected using electronic CRFs (eCRFs). Data collection will be undertaken by designated study staff involved in the study. Only those individuals who have been trained on the CRF/eCRFs and/or other document completion and have been authorized by the Site PI may complete eCRFs and other study specific documentation. The research data collected on the eCRFs will be captured using devices i.e. tablets and/or laptops used by study staff. Where there's internet connectivity, collected data will be stored directly onto the central server and where there is no/unreliable connectivity, data will be stored locally on the tablet and later synchronized to the central servers at MRCG Fajara. Field staff will be trained to use of the REDCap mobile application and clinicians will be trained to use the REDCap web portal. The data from the accelerometer used for monitoring PA will be directly downloaded on the tablet by the trained research staff on a weekly basis.

### **11.4. Data quality and standards**

Review of data collection tools against the protocol will occur prior to database build by the Data Developer to ensure all data is being captured, at the correct time points, and in a format conducive to the proposed statistical analysis. Site based staff will be fully trained in conducting any study assessments and subsequent completion of the CRF and a Site delegation log will be maintained. Study staff will be trained in the use of Redcap. Principles of GCP will be adhered to and all training will be documented. To ensure standardisation of processes, standard operating procedures with respect to trial management, quality assurance, data management, IT & security, and statistics will be adhered to. The entry screens will be designed with range checks, skip patterns and validations to assist/guide data collectors and to ensure high level accuracy. Multiple choice options will be employed when and where applicable. Mandatory field checks and other computable data will be pre-populated to eliminate errors. The data manager will conduct periodical data cleaning routines to flag data queries that were not picked up in the earlier stages. All data queries raised by the data manager will be answered by the local PI or a delegated senior member of the study team involved in the generation of the data in question normally within one week. All changes to any CRFs or databases will be governed by a change control SOP, ensuring that all sites are using the same version of both CRFs and databases.

### **11.5. Managing, storing and curating data**

Paper records will be stored securely in locked rooms or cabinets, according to standard filing and archiving procedures by both centres. Electronic data collected at both sites (India and The Gambia) will be centrally monitored and stored by the MRC Unit, The Gambia. The database will be housed on a secure network server with no direct physical access to it by project team members. Access to the system is via a web interface that will be hosted on the Fajara production server (<https://redcap.mrc.gm/redcap/redcap>) managed by the IT department. All data stored in REDCap will be formatted in XML when exported using Clinical Data Interchange Standards Consortium Open Data Model (CDISC ODM) export format which is vendor neutral,

Date and version No: 18th July 2019, Version 4.2

platform independent format for interchange and archive of clinical trials data. The database will be backed up as part of the IT department's backup routine and disaster recovery process. ICF will be maintained locally in the respective study centres in secure cabinets with limited access to authorized study staff only. The ICF will be retained for a period of 5 years after study completion and publication of primary results. Other PID (personally identifiable data) will be stored indefinitely for the purpose of future follow-up studies.

#### **11.6. Data preservation strategy and standards**

At the end of the study (when the last participant enrolled in the study completes the delivery visit) the database will be locked and all the electronic study data will be housed in the REDCap Database server until the first publication is made following which the data will be sent to the electronic data archives for long-term preservation. The locked database will have very highly controlled access as detailed in the Archives Research Records Management Policy ([POL-ARM-001](#) - Available on request). All electronic records will be kept indefinitely and all paper records and lab books will be stored in the on-site temperature and pest controlled MRC as dictated by the MRC Unit The Gambia's SOPs on Data Retention and Destruction ([SOP-ARM-005](#)) and formal information/data security standards. The study will be run in compliance with the [MRC Corporate Information security Policy](#) and the MRC Unit The Gambia's INFORMATION AND COMMUNICATION TECHNOLOGY SECURITY [POL-INT-001](#) available on the MRC Gambia intranet (Available on request).

#### **11.7. Main risks to data security**

Main risk to confidentiality is the personal information on subjects kept by the local-PI for study follow up verification purposes. These will be kept separate from the actual research data and not available to the study staff so that no linkages of personal data to study records would be easily made. The research data will be stored in a limited access, password protected database so that only staff who have the required permissions can view the study records. Personal information will be available only to study PI and designated staff involved in contacting the participants either telephonically or by home visits.

#### **11.8. Suitability for sharing**

The data generated within the study will be suitable for sharing in an anonymised format. The data will be in a format that is suitable to share with other interested researchers. All data meant for sharing will be anonymised/de-identified by removing all individual-level participant data (IPD) and will be archived on the servers of the Archives department of MRCG. Data sharing will be in agreement with the MRCG as outlined and governed by the Data Sharing Policies i.e. Data Sharing Policy v2.2 and MRC Policy and Guidance on Sharing of Research Data from Population & Patient Studies. The regulations will also adhere to the University of Oxford data policy guidelines. PID will not be shared across organisations.

#### **11.9. Access to Data**

Direct access will be granted to authorised representatives from the University of Oxford and any host institution for monitoring and/or audit of the study to ensure compliance with regulations.

Date and version No: 18th July 2019, Version 4.2

### 11.10. Data Handling and Record Keeping

All study data will be downloaded from RedCap into an Excel spreadsheet. The participants will be identified by a unique study specific number in any database. The name, addresses and any other identifying details will NOT be included in any study data electronic file. All data will be fully described in the Excel data dictionary which will include the variable name, variable description, label (if different from description), database table name, data grouping information, type of data (string, integer, real etc.), data codes and decodes and any validation rules used. All data stored in REDCap will be formatted. Person data and research data will not be linked. After completion of the study, research data will be stored indefinitely at central servers in MRC, Fajara, The Gambia. PID including ICF will be stored for a minimal period of 3 years after study completion and destroyed subsequently as per local data management policies. All data management processes and procedures will be governed by the library of MRCG's data management standard operating procedures.

## 12. COMMITTEES STRUCTURES

The study will be conducted in accordance with the current approved protocol, Good Clinical Practice (GCP) regulations and standard operating procedures (SOPs).

### 12.1. DATA SAFETY MONITORING COMMITTEE (DSMC)

An independent Data Safety Monitoring Committee (DSMC) has been set up to review the progress of the trial and provide feedback to the Trial Steering Committee (TSC).

The DMC will be responsible for reviewing

- (i) general study progress (recruitment, compliance, loss to follow-up)
- (ii) clinical study safety data and assess and/or adjudicate all events of deaths
- (iii) the GDM event rate and key secondary/safety outcomes
- (iv) results of the interim analysis. The DSMC includes the following members (To address: chair of DSMC, Report preparation, confirm meeting timelines).

The DMC will review and analyze, on a regular basis, unblinded safety data throughout the study.

An independent DSMC with members who are independent from the Sponsor and the investigators for the PRIMORDIAL study comprises of experts in clinical trials/epidemiology, biostatistics and obstetrics and include the following members

| Name (Designation)                                               | Address                                                                                             | Email                                                        |
|------------------------------------------------------------------|-----------------------------------------------------------------------------------------------------|--------------------------------------------------------------|
| [name]
(Paediatrician & Postdoctoral Research Fellow) | MRC Unit The Gambia at the London School of Hygiene & Tropical Medicine, Fajara, Banjul, The Gambia | [contact]             |
| [name]
(Biostatistician)                         | MRC-LEU, University of Southampton, UK                                                              | [contact] |

Date and version No: 18th July 2019, Version 4.2

|                                     |                                                                      |                                                                          |
|-------------------------------------|----------------------------------------------------------------------|--------------------------------------------------------------------------|
| [name]
(Obstetrician) | Nuffield Department of
Obstetrics and Gynaecology,
Oxford, UK. | [contact] |
|-------------------------------------|----------------------------------------------------------------------|--------------------------------------------------------------------------|

Meetings will be held by skype prior to start of the recruitment and then 6-monthly thereafter. The study protocol will be approved by the DSMC prior to enrolment. Any subsequent updates and implications will be reviewed periodically.

